**Cognitive DT outcomes**		
Cognitive-task accuracy	Assesses the percentage of cognitive task responses that are correct in dual-task conditions	To compare whether cognitive performance when turning is impaired in people with mTBI
Number of correct responses per second	Assesses the overall number of correct responses, divided by the overall time in seconds	

* *These measures will involve assessment of both the mean and the variability (i.e., standard deviation)*.

**Figure 1 F1:**
[figure not shown]
Overview of the three primary clinical turning tasks for this study protocol. Left: The 1-min walk (1MW) test is performed by walking at one's self-selected pace back and forth between two lines for 1 min; turns are assessed at the end of the walk, and all turns are 180°. Center: The modified Illinois Agility Test (mIAT) is a condensed version of the Illinois Agility Test and completed at one's maximum running speed; turns are assessed throughout the course and include 180° turns at the ends and shallower slalom turns in the middle. Right: The custom clinical turning course (CCTC) was designed to fit in a small hallway or large examination room and is completed at one's comfortable walking pace; turns are evaluated throughout the course and include 45°, 90°, and 135° turns representative of daily life.

#### Primary Outcome Measures—Predictive Capacity

To assess the capacity of DT turning measures to predict performance in a civilian ambulatory task (CAT), participants will navigate through an uncontrolled pedestrian environment while wearing inertial sensors as shown in Figure 1. A walking route of standardized length will be established at each site for participants to walk around the testing location. Common elements at each site's walking route will be written instructions and landmark-based directions to follow (e.g., take the second set of doors on your right). Each site's walking route will require participants to ambulate around public areas and will take ~7 min to complete. Participants will be required to navigate through crowded hallways, ascend and descend stairs, and scan for pedestrian traffic. A trained research assistant will accompany the participant throughout the entire route and provide verbal commands. The research assistant will remain behind the participant to not interfere with the navigation, but close enough to assist the participant in case of a loss of balance. Secondary landmarks will be known by the research assistants. If the participant misses a landmark, the research assistant will notify the participant once he/she reaches the secondary landmark, and the research assistant will instruct the participant that he/she traveled the wrong way and reread the instruction. The route will end in the initial testing area. The primary outcome of the CAT will be the time required to complete the route. Secondary outcome measures will include the peak head and trunk turning velocity, the head–body coordination throughout the course, and the number of landmarks identified and missed.

To assess the capacity of DT turning measures to predict performance in a military-relevant task, participants will complete a simulated urban patrol task (SUP, Figure 2). During the SUP task, participants will navigate an environment containing two small rooms separated by a doorway. The environment will be created using portable partitioning boards to compartmentalize a medium-sized clinical or laboratory space. Each compartmentalized room within the environment will contain five 5-cm diameter targets, surrounded by LED lights. The targets will be placed in areas that are not visible from the adjoining compartment. The LED lights surrounding each target will denote either hostile (illuminated red) or friendly (illuminated blue) targets.

**Figure 2 F2:**
[figure not shown]
Overview of the Simulated Urban Patrol (SUP) task. **(A)** Bird's-eye view of the compartmentalized rooms including one configuration of hostile (red) and friendly (blue) targets. Some targets were configured to require multiple shots to clear; these targets are denoted with three red ***. **(B)** Example image of a hostile target that required three shots to clear. With each shot, 1/3 of the target's LEDs turn off; participants are instructed to completely clear all LEDs on the hostile targets. **(C)** Example image of a friendly target turning white when tagged indicating an incorrect shot.

Participants will be instructed to enter the environment and secure the area as quickly as possible by clearing all hostile targets without harming friendly targets. Participants will use a mock weapon with a trigger-activated laser (i.e., laser gun) to clear targets. To clear hostile targets, participants will need to accurately scan each room and tag the hostile target with their laser. Each target will contain infrared-sensing diodes that will identify when the target was tagged with the laser. Upon tagging each target with a laser, the LEDs surrounding the hostile targets will turn off, while the LEDs surrounding the friendly targets will turn white (indicating an incorrect shot). Following the task, participants will also be asked to recount the number of hostile targets and number of friendly targets in each room. The primary outcome of functional performance for the simulated SUP task will be a throughput score calculated using the Comstock method (67), which allows unlimited rounds and penalizes shooting at the wrong target twice the score of shooting at the correct target (i.e., shooting a friendly target is twice as bad as missing a hostile target). Therefore, each trial will have a maximum number of possible accuracy points: Possible points = 2 * (Number of friendly targets) + 1 * (Number of hostile targets). The final accuracy score will be Accuracy score = Possible points – 2 * (Number of tagged friendly targets) – 1 * (Number of untagged hostile targets). The final throughput score will then be calculated by dividing the accuracy score by the time to complete the task: Throughput = Accuracy score/Completion time. Secondary outcomes will include objective measures of movement, including peak head and trunk turning velocity and head–body coordination, target accuracy, and the accuracy of the hostile / friendly target recall.

#### Sample Size

Sample size calculation and power analysis were based on Hedge's *g* effect sizes determined through preliminary data on turning in people with mTBI (21); we observed a range of Hedge's *g* effect sizes of −1.09 to −1.32 between the peak lumbar turn velocity of healthy controls and people with mTBI and residual symptoms when performing 90° turns. With 50 civilian participants per group and the midrange effect size from our preliminary work, we will have 90% power to detect differences in peak lumbar turning velocity between healthy controls and people with mTBI with a two-tailed 0.01 significance level if we observe at least 65% of the effect size we observed previously (*g* = −1.20). For the second goal, the power analysis was based on the correlation between clinic-based peak turning velocity and the duration of walking bouts, a common measure of daily ambulatory function, exhibited during daily, unmonitored activities at home (Pearson ρ = 0.362, data obtained from DoD #W81XWH-15-1-0620). With 140 planned participants (100 civilian participants and 40 active-duty participants), we will have 97% power to detect a correlation between the lumbar turning velocity measured in the clinic and daily function with a two-tailed 0.01 significance level if we observe the same effect size. Power calculations were performed in G^*^Power 3.1.9.2 (68).

#### Secondary Outcome Measures

Secondary outcome measures of symptomology, cognition, static balance, and clinical measures of mobility are provided in Table 2. Participation level outcomes will be assessed using the Neurobehavioral Symptom Inventory (NSI) (69), Dizziness Handicap Inventory (DHI) (70), and Quality of Life after Brain Injury (QOLIBRI) questionnaires (71). Clinical assessments of activity level will include postural sway during static quiet standing, the Functional Gait Assessment (FGA) (72), and the High Level Mobility Assessment Tool (HiMAT) (73–75). Assessments of body function and structure will include the Vestibular Ocular Motor Screening (VOMS) (76) and the Automated Neuropsychological Assessments Metrics (ANAM) (77). In agreement with the Common Data Elements (CDE) recommendations, covariates aligning with the National Institute of Neurological Disorders and Stroke and Federal Interagency Traumatic Brain Injury Research CDEs will also be recorded. Covariates and confounders will include (1) significant medical history and mTBI history based on a modified version of the Ohio State University TBI Identification Method (prior mTBIs, loss or alteration of consciousness, length of posttraumatic amnesia) and (2) posttraumatic stress disorders (PTSD) using the PTSD Checklist for Civilians and PTSD Checklist for Veterans (78, 79). Military Occupational Specialty (for enlisted and warrant officers) or Area of Concentration (for commissioned officers) for Army participants, Air Force Specialty Code for Air Force participants, and Navy Enlisted Classification (for enlisted SMs) or Commissioned Officer Designator (for commissioned officers) for Navy participants will be collected to further characterize the active-duty military sample.

**Table 2 T2:** Secondary outcome measures for phase 1.

**Outcome measures**	**Description**	**Purpose**
**Participation level, ICF**		
*Questionnaires*		To determine the criterion validity of objective measures of DT turning with perceived handicap, symptom severity, and quality of life
Neurobehavioral symptom inventory	Assesses self-perceived symptoms associated with mTBI	
Dizziness handicap inventory	Assesses self-perceived handicap imposed by dizziness	
Quality of life after brain injury	Assesses the effects of TBI on quality of life	
**Activities level, ICF**		
*Clinical assessments of activities*		To assess the value of objective measures of DT turning over current clinical assessments of activities
Static sway (ML-RMS of sway)	Assesses static postural stability	
Functional gait assessment (total score)	Assesses dynamic balance by measuring performance on simple and complex gait tasks	
High level mobility assessment tool (total score)	Assesses dynamic balance by measuring performance on rapid and challenging mobility tasks	
**Body functions and structures level, ICF**		
*Clinical assessments of body functions and structures*		
Vestibular ocular motor screening (VOMS)	Assesses ocular–motor function and the provocation of symptoms	To compare the diagnostic accuracy of objective measures of DT turning to current clinical assessments of body functions and structures
Automated neuropsychological assessment metrics (ANAM)	Assesses cognitive domains of attention, memory, reaction time, processing speed, and executive function	

#### Statistical Analysis

To evaluate the capability of objective, DT turning measures to discriminate between healthy controls and people with mTBI, we will construct receiver operating characteristic (ROC) curves using each objective turning outcome and clinical assessment of activity. The area under the ROC curve (AUC) will be calculated, and AUC confidence intervals will be generated through a bootstrapping procedure. We will compare the AUCs and confidence intervals between each objective turning measure and clinical assessment of activity using tests of equality and a 0.05 significance level with Holm-Bonferroni corrections to adjust for multiple comparisons.

To assess the capacity of DT turning measures to predict performance in civilian or military-relevant tasks, we will use Pearson correlation coefficients and linear regression models. Pearson correlation coefficients will compare the linear relationship between objective turning outcomes and the primary outcome of task completion time during the CAT and throughput during the SUP tasks within participants with mTBI, healthy control participants, and all participants together. To determine how changes in objective turning measures correspond to changes in functional performance, linear regression models will be built for each objective turning measure that was significantly associated with functional performance. The primary outcomes for the civilian and military-relevant tasks will be modeled as the dependent variable. To account for potential differences in performance between civilians and active-duty SMs, a group effect will be included as a covariate. Beta coefficients will be interpreted to identify the relative change in objective turning measures that are associated with changes equal in magnitude to 1 standard deviation of the healthy control participants' performance.

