### Phase 1: Diagnostic Accuracy and Predictive Capacity of Turning Measures

#### Participants

Phase 1 will include approximately 50 civilians with persistent symptoms from mTBI, 50 civilian healthy controls, and 40 active-duty SM healthy controls. Three non-military sites (OHSU, UU, CKRC) will test civilians. A fourth military site (FSH) will enroll and test 40 active-duty SM healthy controls across a range of military experience and ability levels.

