#### Inclusion and Exclusion Criteria

Participants may be active duty (at FSH), veterans, or nonveterans and must (1) have a diagnosis of mTBI based on Veterans Affairs/Department of Defense (VA/DoD) criteria (61, 62), (2) be between 18 and 50 years old, and (3) be outside of the acute stage (>3 weeks postconcussion) according to the VA/DoD clinical practice guidelines (63) but within 3 years of their most recent mTBI and still reporting symptoms. Control participants must have no history of mTBI or be more than 7 years removed from their most recent mTBI and no reported residual symptoms. All participants must (1) not have had or currently have any other injury, medical, or neurological illness that could potentially explain balance deficits (e.g., central or peripheral nervous system disease, stroke, greater than mild TBI, lower extremity amputation, recent (<6 months) lower extremity or spine orthopedic injury requiring a profile); (2) meet criteria for moderate to severe substance-use disorder within the past month, as defined by *Diagnostic and Statistical Manual of Mental Disorders, Fifth Edition* (64); (3) display behavior that would significantly interfere with validity of data collection or safety during the study; (4) be in significant pain during the evaluation (7/10 by patient subjective report); (5) be a pregnant female (balance considerations); or (6) be unable to communicate in English.

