### Secondary Statistical Analyses

To evaluate if turning outcomes have added value over standard clinical assessments of physical function, base multivariate logistic regression models will be constructed for each clinical assessment of physical function (e.g., FGA, HiMAT). A “base + 1” logistic regression model will be built by adding the objective turning measure with the highest AUC as described above. ROC curves will be constructed for the base and “base + 1” models, and the AUC calculated and compared using likelihood ratio tests. If the AUC from the “base + 1” model is greater than the AUC of the base model, then the process will be repeated iteratively—the outcome measure with the next largest univariate AUC will be added to the “base + 1” logistic regression model to create a “base + *n*” model until the addition of outcomes does not significantly change the AUC.

To evaluate if objective turning measures will be associated with impairments in ICF model components, including body functions and structures, activities, and participation domains, Pearson and Spearman correlation coefficients will be implemented separately within healthy civilian control participants, healthy active-duty control participants, and civilians with mTBI. Linear regression models with ICF impairments (Table 2) as dependent outcomes and main effects of objective turning outcomes, group, and the group ^*^ turning outcome interaction will assess whether the association between objective turning outcomes and ICF function varies by group through the interaction term. A 0.05 significance level will be used with stepwise Holm-Bonferroni corrections to adjust for multiple comparisons.

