### Refinement of Tasks and Outcomes for Future Clinical Use

To reduce the number of tasks and outcomes, a variable selection procedure will be implemented. First, objective turning outcomes for each task will be ranked according to their (1) AUC in differentiating people with mTBI from healthy control subjects, (2) correlation with functional performance in the civilian-relevant task, (3) correlation with functional performance in the military-relevant task, and (4) ratio of mean effect of rehabilitation over minimum detectable change. Outcome–task combinations will then be ordered according to the sum of their ranks across these four categories, where a lower total is better. The outcome, and associated task, with the lowest total sum will be identified and put forward in future applications and clinical training tools. Additionally, a civilian-specific task/outcome combination will be identified by summing the ranks, but excluding the rank corresponding to the correlation with functional performance in the military-relevant task. A military-specific task/outcome combination will be identified similarly, but summing all ranks except the correlation with functional performance during the civilian-specific task.

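### The patrol-task correlations that screen and rank turning measures are not adjusted for service status, so a service-member/civilian difference on both variables can count as predictive capacity

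*Protocol article*

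**What the plan says.** **Sample.** Phase 1, Participants plans "approximately 50 civilians with persistent symptoms from mTBI, 50 civilian healthy controls, and 40 active-duty SM healthy controls". The mTBI group is therefore civilian, the healthy controls number 90 and the whole sample 140.

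**Screen.** Phase 1, Statistical Analysis correlates each turning outcome with civilian-task time and with "throughput during the SUP tasks within participants with mTBI, healthy control participants, and all participants together". It then says that "linear regression models will be built for each objective turning measure that was significantly associated with functional performance".

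**Adjustment.** It enters at that second step: "To account for potential differences in performance between civilians and active-duty SMs, a group effect will be included as a covariate".

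**Contrast.** For the ICF outcomes, Secondary Statistical Analyses takes the correlations "separately within healthy civilian control participants, healthy active-duty control participants, and civilians with mTBI".

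**Ranking.** Refinement of Tasks and Outcomes ranks each outcome-task combination on four criteria, one being "3) correlation with functional performance in the military-relevant task". That rank also counts in the military choice: "A military-specific task/outcome combination will be identified similarly, but summing all ranks except the correlation with functional performance during the civilian-specific task".

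**Conditional split.** Secondary Statistical Analyses also compares turning between healthy service members and healthy civilians, with Holm-Bonferroni adjustment. Where an outcome differs significantly, the two control groups are to be kept apart in later analyses of that outcome.

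**The concern.** The plan recognises that civilians and service members may perform differently, but it deals with this only after the unadjusted correlation has decided which measures are modelled. The ranking also uses a correlation, not the adjusted coefficient, so the later covariate cannot undo a rank.

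The patrol task involves clearing rooms with a mock weapon, so a service-member advantage in throughput is plausible. The Discussion itself offers faster turning as an example of how military populations might differ. If both hold, a turning measure correlates with throughput in a mixed set even when it says nothing about how well one service member performs relative to another. All service members are tested at one site, so the raw correlation can also absorb site differences.

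At stake is the choice of measure for clinical training tools, in particular the military-specific choice.

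**Working it through.** **1. The plan's own figure.** Sample Size gives 97% power for r = 0.362 with N = 140, two-tailed 0.01. By Fisher's z: Φ(atanh(0.362)·√137 − 2.576) = 96.9%. It reproduces. It is computed on civilians and service members pooled.

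**2. Correlation induced by a group difference alone.** Assume no association inside either group. Let service members differ from civilians by d1 (turning) and d2 (throughput) in within-group SDs, and treat the mTBI civilians as like the other civilians. With p the share of service members and q = p(1 − p):

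r = q·d1·d2 / √[(1 + q·d1²)(1 + q·d2²)]

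- All participants: q = (40/140)(100/140) = 0.2041
- Healthy controls: q = (40/90)(50/90) = 0.2469

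When d1 = d2 = d this is q·d²/(1 + q·d²):

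- 0.5 SD: 0.0510/1.0510 = 0.049 (all); 0.0617/1.0617 = 0.058 (controls)
- 1 SD: 0.2041/1.2041 = 0.170 (all); 0.2469/1.2469 = 0.198 (controls)
- 1.5 SD: 0.4592/1.4592 = 0.315 (all); 0.5556/1.5556 = 0.357 (controls), close to the planning value of 0.362

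**3. How often the screen opens.** Statistical Analysis gives no significance level for these correlations; its 0.05 with Holm-Bonferroni belongs to the AUC comparisons. Sample Size uses 0.01 for this goal. Both are shown, from 20,000 simulated trials.

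| Difference on both | All 140: p<0.05 / p<0.01 | 90 controls: p<0.05 / p<0.01 |
|---|---|---|
| 0.5 SD | 9% / 2% | 9% / 2% |
| 1 SD | 52% / 29% | 48% / 24% |
| 1.5 SD | 98% / 91% | 96% / 85% |

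The correlation adjusted for service status is significant at 0.05 in about 5% of trials throughout.

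**4. If the conditional split did apply.** Take its first Holm step over an assumed 60 outcome-task tests. It triggers in 15% of trials at a 0.5 SD turning difference, 62% at 0.8 SD and 89% at 1 SD. Trials in which the all-participant correlation has p<0.05 and the split has not triggered:

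- 0.5 SD on both: about 7%
- 1 SD on both: about 3%
- 1.5 SD on both: about 0%
- 0.5 SD turning with 1 SD throughput: about 13%
- 0.5 SD turning with 1.5 SD throughput: about 22%

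**5. Cost of adjusting.** One degree of freedom: Φ(atanh(0.362)·√136 − 2.576) = 96.8%, if the within-group correlation is 0.362. Within the 40 service members alone, power at 0.01 is Φ(atanh(0.362)·√37 − 2.576) = 39%, and the SE of r near zero is about 1/√39 = 0.16.

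**The case against.** **The conditional split is a safeguard.** A reader might infer that the correlation is never taken within service members. The article does not support that. Step 4 shows that, if the split reached the screen and the ranking, it would remove most of the artefact when the turning difference is large. But it sits among the secondary analyses, is not stated to reach either step, depends on a significance test, and leaves 13% to 22% when the turning difference is moderate and the throughput difference larger. It would also have some measures ranked on split samples and others on pooled ones, so their ranks would not be comparable.

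**The regressions correct the screen.** In part they do: a measure that passes only through a group difference should have an adjusted coefficient near zero. The ranking, however, does not use that coefficient.

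**The ranked correlation is not named.** This stands as a limit. The mTBI correlation is civilian only and free of the artefact, though it cannot show prediction among service members. The second goal was sized on all 140, which points to the pooled set but does not settle it.

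**No wrong selection is shown.** A reader might infer that the wrong measure will be chosen. That does not follow. Ranks are relative, so a shift common to all measures need not reorder them, and this criterion is one of four (three in the military choice). Only measures on which the groups differ to different degrees would be reordered.

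**Veterans.** The eligibility text reads "Participants may be active duty (at FSH), veterans, or nonveterans", and a reader might infer that veterans will be miscounted as untrained. The article gives neither a veteran count nor their coding, which may properly be left to the analysis plan.

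**Conclusion.** The point holds in limited form. The screening correlations are unadjusted, two of the three sets mix civilians with service members, and the ranking uses a correlation with neither set nor adjustment named. A difference between the populations on both variables can therefore be credited as predictive capacity.

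The size rests on differences that the article does not give. With no within-group association assumed, the effect is close to negligible at 0.5 SD on both variables and material from about 1 SD, where roughly half of trials would pass at 0.05 and a quarter at 0.01. These rates also assume that the conditional split does not apply to the screen. The article leaves that open, as it does the screen's significance level. The effect on the final selection is possible but not quantified. The change is worth making before analysis because the plan already contains the covariate that removes the problem.

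**What to change.** 1. For every turning measure, not only those that pass a raw screen, compute the partial correlation with patrol throughput adjusted for service status. Use it for both the screen and the ranking.
2. Report the correlation within the 40 service members for each measure as an estimate with its interval, not as a test.
3. In Refinement of Tasks and Outcomes, name the correlation and the set that are ranked. State that the conditional split of control groups does not change that correlation measure by measure.
4. State the significance level for the screen.

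This changes analysis wording only and costs one degree of freedom. The downside is that the reported correlation may be smaller than the raw pooled one.

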If we find the DT turning performance can improve diagnostic accuracy of standard clinical assessments, is associated with functional performance in ecologically relevant tasks, and is responsive to rehabilitation, the results of this study will motivate rapid adoption of DT turning assessments in mTBI rehabilitation and RTD decisions. However, we anticipate that a single outcome measure may not satisfy all of these criteria. By instrumenting various body segments with wearable inertial sensors, we will simultaneously capture multiple outcome measures, each quantifying distinct aspects of movement (Table 1), for each task. Current clinical assessments of physical function lack this feature; they provide only one global score. However, clinical assessments with too many outcomes can become unguided. Our procedure to refine the selection of tasks and outcomes will rank outcomes based on their individual attributes (e.g., diagnostic accuracy, predictive capacity, sensitivity to change), as well as their overall combined attributes. These rankings will then guide the selection of tasks and outcomes that are ultimately recommended for clinical implementation.

Occupational demands and physical capabilities vary widely between and within civilians and military populations. Thus, adequate performance on the proposed turning tasks may be viewed as the bare minimum standard for RTD decisions. Because of the vast heterogeneity in occupational demands and physical capabilities both within and outside of the military, the current study is not designed to determine how performance varies by these factors. However, we anticipate addressing the extent to which performance differs between general civilian and military populations. If military populations perform differently (e.g., turn faster), it supports the use of population-adjusted normative ranges. Yet, even population adjusted normative ranges fail to address the variability within each subset due to occupation or physical health. Accordingly, the results of this study may be seen as a stepping stone for more individualized, and perhaps more complex, RTD assessments based on specific occupational duties.

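### The predictive-capacity (Goal 2) correlations are gated on significance, but the analysis paragraph gives no alpha, no multiplicity adjustment and no deciding measure, turning course or population

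*Protocol article*

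**What the plan says.** The second paragraph of Statistical Analysis (Phase 1) plans Pearson correlations between the objective turning outcomes and two criteria, CAT completion time and SUP throughput, "within participants with mTBI, healthy control participants, and all participants together". It continues: "linear regression models will be built for each objective turning measure that was significantly associated with functional performance". The slopes are then interpreted as the change in turning that corresponds to one standard deviation of control performance. The paragraph contains no significance level and no adjustment.

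Elsewhere the article is explicit. The AUC comparisons in the preceding paragraph, and the ICF associations and the active-duty versus civilian comparison under Secondary Statistical Analyses, each have 0.05 with Holm-Bonferroni.

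Sample Size attaches a different level to Goal 2: "we will have 97% power to detect a correlation between the lumbar turning velocity measured in the clinic and daily function", at a two-tailed 0.01, from "Pearson ρ = 0.362". It starts "With 140 planned participants (100 civilian participants and 40 active-duty participants". The criterion behind that correlation is the duration of walking bouts at home, which is neither CAT time nor SUP throughput.

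Table 1 lists one primary outcome, peak lumbar turning speed. Primary Outcome Measures—Predictive Capacity names one primary outcome for CAT and one for SUP.

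The Discussion treats the result as one of three conditions: if turning improves diagnostic accuracy, "is associated with functional performance in ecologically relevant tasks, and is responsive to rehabilitation, the results of this study will motivate rapid adoption".

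**The concern.** Goal 2 is one of the study's main goals, with two hypotheses and its own power statement. Yet it is tested with less error control than the secondary ICF and service-status analyses. Because significance is the operative gate, the reader has to know what counts as significant. Two levels are in play, 0.01 from Sample Size and 0.05 from the other analysis families, and the paragraph chooses neither.

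Nor does the paragraph say which turning measure, course (1MW, mIAT or CCTC) or population settles either hypothesis. A nominally significant cell anywhere in a large grid could therefore be presented as support. In addition, slopes reported only when the correlation passed a test are on average too far from zero.

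**Working it through.** **1. The plan's own power figure.** Inputs from Sample Size: ρ = 0.362, n = 140, two-sided alpha 0.01. Fisher z: power = Φ(atanh(ρ)·√(n − 3) − z). Here atanh(0.362)·√137 = 4.438 and z = 2.576, so power = Φ(1.862) = 96.9%. The stated 97% is reproduced.

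**2. Size of the grid.** Table 1 has four starred measures, each taken as mean and SD (8), plus two unstarred (2), giving 10 objective turning outcomes. With 3 dual-task courses, 2 criteria and 3 populations: 10 × 3 × 2 × 3 = 180 tests. Adding the single-task conditions gives 360. The article does not state a count; this is my reading of its tables.

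**3. Family-wise error under a global null.** Assumptions: 50 mTBI and 90 controls, the pooled set overlapping both; everyone performs both CAT and SUP; CAT–SUP correlation 0.5 in absolute value (0.4 gives nearly the same results); a common correlation of 0.3 to 0.8 between turning measures. The documents give none of these correlations. Results by simulation:

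| Tests | Per-test 0.05 | Per-test 0.01 |
|---|---|---|
| 180: all outcomes, three dual tasks, three populations | about 0.7 to 0.99 | about 0.3 to 0.67 |
| 18: lumbar speed, three dual tasks, three populations | 0.35 to 0.48 | 0.10 to 0.15 |
| 6: lumbar speed, three dual tasks, all 140 | not used here | about 0.04 to 0.06 |

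The lower end of each range belongs to correlation 0.8, the upper end to 0.3. In the 180-test grid, 180 × 0.05 = 9 false associations are expected at 0.05, and 180 × 0.01 = 1.8 at 0.01.

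**4. What the unresolved alpha changes.** The critical |r| is t/√(n − 2 + t²).
- n = 140: 0.166 at 0.05, 0.217 at 0.01.
- n = 50 (mTBI only): 0.279 at 0.05, 0.361 at 0.01.

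In the mTBI group, an observed correlation equal to the planning value of 0.362 sits on the 0.01 boundary. Power there for a true ρ of 0.362 is 74% at 0.05 and 51% at 0.01.

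**5. Selection on significance.** With a true ρ of 0.2 and alpha 0.05, the mean r among significant results is 0.245 at n = 140 and about 0.36 at n = 50. With ρ = 0.362, n = 140 and alpha 0.01 it is about 0.367, so the inflation is negligible if the planning assumption holds.

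**6. Power after the fix.** Six tests under Holm at 0.05 have a first step of 0.05/6 = 0.0083, z = 2.638. Power = Φ(4.438 − 2.638) = Φ(1.800) = 96.4%.

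**The case against.** The strongest reply is that the article says more than its analysis paragraph. Sample Size gives Goal 2 a two-tailed 0.01. Table 1, the CAT and SUP definitions and the power statement together point to peak lumbar turning speed against two criteria in all 140, and the hypotheses are confined to dual-task conditions. Read that way, the family-wise error is near 5% already. This stands, and it rules out saying that Goal 2 has no alpha anywhere or no indicated contrast. It does not close the gap: the analysis paragraph neither repeats the 0.01 nor gives lumbar speed, a course or a population deciding status, and its gate applies to every turning measure.

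A reader might also infer that a chance finding is nearly certain and would lead to adoption or to the choice of the recommended outcome. The documents do not support that. At 0.01 even the full grid gives roughly 0.3 to 0.67. The Discussion requires three conditions jointly. The rule in Refinement of Tasks and Outcomes for Future Clinical Use ranks outcomes by size of correlation, among other criteria, and uses no p-value.

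A condensed article may leave multiplicity detail to a fuller plan. That lowers the weight of a bare omission, but here the article states the rule for three other families and prints an alpha for Goal 2 that differs from theirs.

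Finally, making the pooled correlation decisive is open to challenge. Sample Size anticipates g of about −1.2 between mTBI and controls in turning velocity, so a pooled correlation may partly reflect group membership. That objection is sound and shapes the fix.

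**Conclusion.** The point holds in limited form. The Goal 2 paragraph sets a significance gate over a large set of correlations without an alpha, an adjustment or a deciding contrast, and leaves the 0.01 in Sample Size unreconciled with the 0.05 used in the other families. Followed as written over about 180 dual-task tests, the chance of at least one false association is roughly 0.7 to 0.99 at 0.05 and 0.3 to 0.67 at 0.01. Restricted to the six pooled lumbar-speed tests that the article hints at, it is about 4 to 6% at 0.01. These figures rest on my test count, a global null and assumed correlations. The consequence is confined to claims that the two hypotheses are supported and to slopes shown only after selection. It should be corrected, and the correction is cheap.

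**What to change.** In the second paragraph of Statistical Analysis:

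1. State one alpha for Goal 2 and reconcile it with the 0.01 in Sample Size.
2. Name the deciding family: mean peak lumbar turning speed in the three dual-task courses, against CAT time and SUP throughput, in the 140 participants, with Holm-Bonferroni at two-sided 0.05.
3. Check that each pooled association holds after adjustment for group (mTBI or control, and civilian or active duty), or report the within-group correlations beside it. The group covariate now planned is described only for the civilian versus active-duty difference.
4. Label all other combinations of outcome, condition and population exploratory.
5. Report the regressions for the pre-named measures whether or not the correlation is significant.

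The cost is wording only, with no new data. Power at ρ = 0.362 and n = 140 becomes about 96% at the first Holm step instead of 97%. The real concession is that nominal hits outside the named family can no longer be claimed as confirmatory.
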